## Introduction

Chronic obstructive pulmonary disease (COPD) is a multisystem disease, primarily affecting the lungs and characterized by incompletely reversible airflow obstruction [1]. COPD is common, affecting 10% of adults worldwide and 14% of Australians aged >40 years [2]. Despite treatment according to guidelines, people with COPD experience a range of symptoms. Breathlessness is often prominent among these and may contribute to physical and psychological distress, and reduced functional status and community participation [1]. Breathlessness is responsible for a high proportion of ambulance presentations, medical admissions, and health care costs [3,4]. However, patients with refractory breathlessness and their caregivers feel that there is a lack of awareness of the symptom burden among health care providers and insufficient provision to address this burden within health care services [2,5,6].

Breathlessness intervention services have been clearly shown effective in reducing the burden of breathlessness for populations with malignant and mixed etiology disease [7]. Existing breathlessness intervention service research primarily targets participants with malignant disease, in Europe, over a 4- to 6-week period, led by clinicians whose expertise is in palliative care [7]. An Australian protocol for a single-blind, randomized, parallel-group study investigating the impact of a breathlessness intervention service on people with COPD has been published; however, the study outcomes are not yet fully reported [8].

The primary aim of this study is to assess whether participants living with COPD will experience reduced breathlessness impact following participation in a bespoke 9-week intervention, the Macarthur Breathless Clinic (MBC), focused on nonpharmacological interventions such as breathing retraining, energy conservation, physical activity, and use of a handheld electric fan. A secondary aim is to monitor participants’ exacerbations, health care use, and rescue medication use after the intervention for comparison with past patterns of disease activity. Furthermore, we will use qualitative methods to assess patient and caregiver experiences.

The hypothesis is that patients with COPD will experience (1) reduced impact of breathlessness (in terms of coping ability, symptom burden, quality of life, and psychological distress); (2) reduced COPD-related health care use; and (3) report a positive consumer experience following participation in the MBC.

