### Recruitment

Clinician referrals will be sought via outpatient services or after stabilization following hospital admission for COPD-related illness. Referrals will be screened by research personnel to ensure eligibility. Previous piloting of this mode of referral and recruitment has demonstrated feasibility for achieving the recruitment target over 12 months.

Where applicable and with patient agreement, carers will be invited to participate in the trial to contribute qualitative data to reflect on their support person role and perceptions of the service.

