### Sample Size

Recruitment target estimation is constrained by limited precedent data, most of which originate from research undertaken in the United Kingdom, studying participant populations, interventions, and outcomes that differ to ours [7,8]. However, pilot data from Westmead Hospital’s Breathlessness Clinic for patients with COPD (similar target population to that proposed in this study) demonstrated statistically significant and clinically relevant outcome improvements in preliminary analysis of only 10 participants [9]. The currently proposed model has been informed by their prior experience. To allow for the substantial losses to follow-up commonly seen in clinical trials in moderate to severe patients with COPD, we have set our recruitment goal at 92 participants, in anticipation of 30% (n=31) discontinuation or dropout.

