#### Statistical Analysis Plan

Descriptive statistics will be applied to the study population to characterize them in terms of demographic and baseline clinical parameters. Normally distributed continuous variables will be expressed as mean (SD), nonparametric variables will be defined by median and range, while categorical variables will be expressed as percentages.

Breathlessness outcomes will be compared across 3 time points: baseline, 9 weeks, and 52 weeks using repeated measures ANOVA. Predictors of response will be sought using linear regression models with sex, forced expiratory volume (FEV) in 1 second, ratio of FEV to forced vital capacity, BMI, Montreal Cognitive Assessment, and baseline anxiety and depression scores as prespecified variables. Health care use measures and exacerbation data for the 12 months prior to MBC enrollment will be compared with the corresponding values for the 12 months after MBC enrollment, using Student 2-tailed *t* tests or nonparametric tests as appropriate. Protocol completer and dropout populations will be compared in terms of baseline characteristics (sex, age, FEV in 1 second, pack years, BMI, CRQ-Mastery subscale, CAT score, and Montreal Cognitive Assessment) to investigate potential selection bias.

Finally, comparison will be made with patients’ baseline data from the year prior to enrollment in the breathless clinic, benchmarked against nonparticipant comparator hospital deidentified patient medical records with (1) ED presentations for reasons of breathlessness, triaged as “shortness of breath—respiratory” or (2) hospitalized with exacerbations of COPD or heart failure as per diagnostic related group assignment. These benchmarking comparisons will use deidentified electronic medical records and will contribute to exploratory analyses undertaken to better understand the health care use of our sample cohort in the context of the overall health care use patterns of our local population “breathless” groups.

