However, this study has several limitations that must be acknowledged. First and foremost is the nonrandomized study design; all recruited participants will receive the intervention and act as their own controls. This design could introduce both time and attrition bias and is a clear limitation on the level of evidence produced. The authors were aware of a randomized controlled trial [8] underway in another Australian center using a similar model to our protocol, and we therefore chose a nonrandomized study design to address clinical need while still demonstrating translatability to a different population and setting. Given that COPD is a chronic and progressive disease, evaluating the impact of breathlessness over time may still yield valuable insights, provided the results are interpreted carefully. While potential mortality among participants with more severe disease may skew study results, on the other hand, worsening disease trajectory may mask benefits when determining results over the longer term. Considering this, even if patients appear to be stable with respect to outcome measures at 12 months, this may actually represent improvement compared with the expected trajectory in COPD, which is one of deterioration. In fact, clinically significant breathlessness is a known marker of poor prognosis for patients with COPD [21], and so our target population will be expected to deteriorate more rapidly than the COPD group as a whole.

The study’s proposed setting, a single metropolitan center situated within a large semirural area, may limit the general applicability of our results. However, the authors are aware of concurrent research on this topic being conducted at other centers and health districts throughout Australia, which should help to address this.

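### The raw 12-month before/after comparison of admissions, bed days and exacerbations keeps the admission that led to referral in the before year, which biases it toward a fall if underlying rates are stable

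*Protocol article*

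**What the plan says.** Recruitment describes two ways in: "Clinician referrals will be sought via outpatient services or after stabilization following hospital admission for COPD-related illness". The share expected from each is not stated.

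Health Care Resource Use Outcomes lists unplanned hospitalizations, their bed days, and COPD exacerbations, including those treated in hospital. ED presentations are counted only when they do not end in hospitalization.

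The Statistical Analysis Plan section compares whole years: "exacerbation data for the 12 months prior to MBC enrollment will be compared with the corresponding values for the 12 months after MBC enrollment", with Student t tests or "nonparametric tests as appropriate". Nothing removes the admission that led to referral or shifts the window. The comparison bears on the second hypothesis, "reduced COPD-related health care use".

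The exclusion criteria bar anyone with a moderate or severe exacerbation within 4 weeks. A benchmark against other patients' records is planned, worded as "baseline data from the year prior to enrollment in the breathless clinic, benchmarked against nonparticipant comparator hospital deidentified patient medical records" and described as exploratory.

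Strengths and Limitations says of the single-arm design: "This design could introduce both time and attrition bias and is a clear limitation on the level of evidence produced". It adds that "worsening disease trajectory may mask benefits when determining results over the longer term". Selection on a recent event is not named.

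**The concern.** A participant referred after a COPD admission is in the study because of that admission. At least one admission, its bed days and its exacerbation are therefore guaranteed in the before count, and no event is guaranteed in the after count. Using participants as their own controls does not help, because selection acts on the same variable that is then compared. This is regression to the mean, and it works in the clinic's favor.

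At stake is the reading of hypothesis 2. A significant fall in admissions could be reported as a benefit when part or all of it comes from how people entered. The drift that the limitations do discuss, disease progression, runs the other way, so a reader is warned only about the bias that would hide a benefit.

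**Working it through.** **Figures in the plan.** No event rate, effect size, SD, alpha or power is given for this comparison, so there is no stated result to reproduce. The only design figures are in Sample Size: "we have set our recruitment goal at 92 participants, in anticipation of 30% (n=31) discontinuation or dropout". (0.30 × 92 = 27.6, not 31; that is a separate arithmetic point.) I use n = 92, and n = 92 − 31 = 61 as a sensitivity case.

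**Assumed inputs, not in the documents.**
- Share referred after admission, f: 25%, 50%, 75%.
- Mean admission rate among outpatient referrals, λ: 0.5, 1, 1.5 per year.
- Between-patient variation: gamma, shape 2. Patients found through an admission have higher rates on average: (2 + 1)/2 = 1.5λ.
- Index admission 6 weeks before enrollment with none in between, leaving 46 earlier weeks. For outpatient referrals the 4-week exclusion leaves 48 weeks.
- No clinic effect, stable rates, two-sided alpha 0.05.

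**Formulas.**

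Before = f × [1 + 1.5λ × 46/52] + (1 − f) × λ × 48/52

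After = f × 1.5λ + (1 − f) × λ

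**Central case (f = 0.5, λ = 1).** Before = 0.5 × (1 + 1.327) + 0.5 × 0.923 = 1.625. After = 0.75 + 0.50 = 1.250. Spurious fall = 0.375/1.625 = 23.1%.

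**Grid.** Means come from the formulas. The last two columns come from 4,000 simulated trials per cell with a paired t test, and show the chance of a significant fall (nominal 2.5%).

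| λ | f | Before | After | Fall | n = 92 | n = 61 |
|---|---|---|---|---|---|---|
| 0.5 | 25% | 0.762 | 0.563 | 26.2% | 39.3% | 27.8% |
| 0.5 | 50% | 1.062 | 0.625 | 41.2% | 93.4% | 81.8% |
| 0.5 | 75% | 1.363 | 0.688 | 49.6% | 100% | 98.6% |
| 1 | 25% | 1.274 | 1.125 | 11.7% | 14.5% | 11.0% |
| 1 | 50% | 1.625 | 1.250 | 23.1% | 60.2% | 45.1% |
| 1 | 75% | 1.976 | 1.375 | 30.4% | 93.5% | 79.0% |
| 1.5 | 25% | 1.786 | 1.688 | 5.5% | 7.4% | 5.9% |
| 1.5 | 50% | 2.188 | 1.875 | 14.3% | 33.9% | 23.3% |
| 1.5 | 75% | 2.589 | 2.063 | 20.3% | 70.1% | 51.1% |

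A Wilcoxon signed-rank test in the central case gives about 59% (1,000 trials), so choosing a nonparametric test does not cure it. A variant with wider between-patient variation (shape 1), a 4-week gap for both routes and n = 61 gives a 21% fall, significant in 43%, for λ = 1 and f = 50%.

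**Where it vanishes or reverses.**
- f = 0: the 4 empty weeks give an apparent rise of 52/48 − 1 = 8.3%.
- f = 10%, λ = 1: 1.063 against 1.050, a fall of 1.3%.
- Break-even, from f(1 − 1.5λ × 6/52) = (1 − f)λ × 4/52: f = 4.0%, 8.5% and 13.5% for λ = 0.5, 1 and 1.5.
- An assumed 20% worsening, λ = 1: at f = 50% the fall shrinks to (1.625 − 1.500)/1.625 = 7.7%, significant in 10.9%; at f = 25% it becomes a 6.0% rise (1.274 against 1.350).

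**With the repair.** Index admission dropped and before-counts divided by at-risk time, n = 92: before and after rates agree within simulation error in all nine cells. A falsely significant fall occurs in 2.0% to 2.9% of trials, and significance in either direction in 4.4% to 5.6%.

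**The case against.** The strongest reply is that the size is unknown. The article gives neither the referral mix nor the admission rate, the weakest cell of the grid shows little inflation, and two features of the plan pull the other way: the 4-week exclusion and the expected deterioration. That stands. A reader might infer that use will appear to fall whatever the clinic does, or that regression to the mean alone would confirm hypothesis 2. The documents do not support either inference; both need a sizeable post-admission share and stable rates. But opposing biases of unknown size do not make a raw comparison interpretable.

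A reader might also extend the point to every health care use outcome. That fails for ED presentations, whose definition leaves out visits ending in hospitalization. It is weaker for exacerbations: these are counted partly by action-plan activation, and Table 2 includes a written exacerbation plan among the clinic's interventions, so capture may rise after enrollment. Only admissions were simulated.

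The nonparticipant records might be thought to supply the missing control. The sentence is ambiguous. Its plain reading sets them against participants' year before enrollment, and neither reading states an expected change over the two windows.

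The limitations already call the design weak evidence and ask for careful interpretation. That is fair, but this mechanism is not named. Nor is it a detail left to a fuller analysis plan, since the article itself fixes the windows and the tests.

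**Conclusion.** The point holds in conditional form. The stated comparison counts the referral-triggering admission on one side only. For unplanned hospitalizations and bed days, and less firmly for exacerbations, it is therefore expected to be biased toward a fall if underlying rates are stable. Under the assumed ranges and n = 92, the spurious fall in admissions is about 5% to 50% and is significant in about 7% to 100% of trials. These figures rest on assumed referral shares, rates, between-patient variation and timing of the index admission. They also treat the 4 weeks before enrollment as free of any admission, although the criterion covers only treated exacerbations. With a post-admission share below roughly 4% to 13%, or with worsening disease, the bias can disappear or reverse.

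This should be fixed, but it does not undermine the study: the outcome is secondary, although it tests hypothesis 2, and the CRQ mastery primary outcome is not touched.

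**What to change.** For unplanned hospitalizations, bed days and exacerbations:

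1. For post-admission referrals, remove from the before window the index admission, its bed days and its exacerbation, together with the interval from it to enrollment. For outpatient referrals, remove the 4-week exacerbation-free period.
2. Compare rates per at-risk person-time in the two windows.
3. Report results separately by referral route.
4. Keep the raw year-on-year comparison as descriptive only.
5. Name selection on a recent event (regression to the mean) among the limitations, beside disease progression.

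ED presentations do not need the index-admission step. Matched before and after windows in the nonparticipant records would add an estimate of expected change. They are optional, and possible only if those records can be linked per patient over both periods, which the article does not state.

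Cost: a change of analysis wording while analysis is still under way, using admission dates from the records review and each participant's referral route. No participant procedure changes. The price is slightly less before time and probably a smaller apparent reduction.

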**Exclusion criteria**
Bed-bound or moribundCognitive impairment that precludes ability to engage and participate in education strategiesCurrent active diagnosis of cancer, substance abuse (other than nicotine dependence), or other uncontrolled medical or psychiatric disorderModerate or severe exacerbation of COPD (defined as an escalation of treatment to include systemic corticosteroids and/or antibiotics [10]) within 4 weeksInsufficient command of the English language to comprehend and engage with interventionsCurrent enrollment in pulmonary rehabilitation program (may participate if still eligible upon program completion or if involved in a long-term maintenance program)

Description of Intervention: MBC

The proposed intervention, the MBC, is a 9-week program to manage chronic refractory breathlessness. The MBC team will include a respiratory physician, occupational therapist, specialist respiratory nurse, and physiotherapist with referrals as needed for dietetic and speech pathology services. The MBC itself will comprise 9 health care interactions of 60 to 90 minutes, with most visits occurring within the patient’s home as outlined in Table 1.

**Table 1 table1:** Macarthur Breathless Clinic 9-week program.

Schedule	Location	Activity
Week 1	Patient’s home	Initial assessment, respiratory nurse
Week 2	Outpatient clinic	Medical assessment by respiratory physician Multidisciplinary team assessment of breathlessness, contributing factors and impacts to develop recommendations and management plan Introduction to nonpharmacologic strategies, including provision and use of a battery-operated handheld fan Fact sheets on managing breathlessness
Week 3	Patient’s home	Physiotherapist
Week 4	Patient’s home	Occupational therapist
Week 5	Patient’s home	Respiratory nurse
Week 6	Patient’s home	Physiotherapist
Week 7	Patient’s home	Respiratory nurse
Week 8	Patient’s home	Final assessments, research assistant
Week 9	Outpatient clinic	Closure and follow-up arrangements, multidisciplinary team

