#### Health Care Resource Use Outcomes

Self-reported exacerbation, emergency department (ED) visit, and hospitalization data will be collected. South Western Sydney Local Health District’s electronic medical records will also be systematically reviewed to verify participant self-reports. Data will be updated at 6 and 12 months from MBC enrollment and will include the annual number of the following:

ED presentations (all presentations), lasting <24 hours, that do not result in hospitalization, as well as breathlessness-related ED presentations, lasting <24 hours, that do not result in hospitalizationUnplanned hospitalizations, including unplanned hospitalizations due to breathlessnessHospital length of stay in bed days (all unplanned hospitalizations), as well as breathlessness-related hospital bed daysExacerbations of COPD counted by patient-reported activation of COPD action plan, along with occasions of prescription of antibiotics and/or corticosteroid for the treatment of symptoms of respiratory exacerbation during hospitalized events

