### Strengths and Limitations

The study’s focus on a homogeneous disease population of patients with moderate to severe COPD will ensure that the results are highly relevant to this specific group. This targeted approach will allow for more precise conclusions regarding the usefulness in this cohort of the intervention being tested. That said, we will recruit a wide range of patients with COPD in terms of severity and exacerbation susceptibility, ensuring broad applicability to this important, and large, patient group. Thus, our results will complement the existing evidence base, as most previously published data include more heterogeneous participant populations; patients with malignant disease, and/or patients with a variety of restrictive and obstructive nonmalignant respiratory disease.

To our knowledge this is the first long-term study protocol for this type of intervention service. By spanning a longer period, an entire year, the study will mitigate the potential confounding effects of seasonal variations in COPD symptoms and exacerbations. This will ensure that the observed outcomes are more likely attributable to the intervention rather than external seasonal factors. Additionally, the proposed intervention requires behavior change, which can take time to implement. By having a longer duration than previous interventions, we hope to enable patients to embed into their routine the suggested nonpharmacological strategies and to thus realize a durable effect beyond the 9 weeks of the program.

The 12-month follow-up period will also provide insight into the durability of the intervention response over a prolonged period. To date, the scientific literature contains few reports of outcomes for this type of intervention extending beyond 2 or 3 months. Showing sustained symptomatic benefits for this type of population with nonmalignant, chronic disease is perhaps much more important than demonstrating a short-term response.

Finally, the use of the CAT as a key assessment tool will underscore the study’s relevance to clinical practice. The CAT is a validated, disease-specific instrument that provides a comprehensive evaluation of COPD symptoms and their impact on patients’ quality of life. This may allow for the MBC to be ranked against other treatment interventions used in COPD, so that any positive study findings can be integrated into existing treatment paradigms, thereby facilitating the translation of research into practice.

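### The 12-month health care use comparison starts at enrollment and so includes the 9-week programme; by itself it cannot show that any reduction persists after the programme

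*Protocol article*

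**What the plan says.** **Aim.** The Introduction sets the secondary aim as monitoring "exacerbations, health care use, and rescue medication use after the intervention for comparison with past patterns of disease activity". The Objective in the Abstract likewise places the reduction in health care use after participation in the MBC.

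**Programme.** The intervention description states: "The proposed intervention, the MBC, is a 9-week program to manage chronic refractory breathlessness". Table 1 lists one contact in each of Weeks 1 to 9. The text after Figure 2 adds case conferences every two weeks during that time.

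**Analysis window.** Under Health Care Resource Use Outcomes, "Data will be updated at 6 and 12 months from MBC enrollment", and the quantities are annual numbers of events. The Statistical Analysis Plan section takes "Health care use measures and exacerbation data for the 12 months prior to MBC enrollment" and says they "will be compared with the corresponding values for the 12 months after MBC enrollment". Both windows are explicitly anchored at enrollment.

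**Durability.** Strengths and Limitations says: "The 12-month follow-up period will also provide insight into the durability of the intervention response over a prolonged period". The paragraph before it expresses the hope of an effect that lasts past the nine programme weeks. Study Design places exacerbations, health care use and durability under the same 12-month follow-up.

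**Breathlessness scores.** These are compared at baseline, 9 weeks and 52 weeks as separate time points.

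**The concern.** The aim and the meaning given to durability concern the time after the programme. The health care use analysis counts events from the day the participant enters it. The annual total therefore pools two different periods: a supervised one with near-weekly contact, and a later one in which participants manage without the team. No section of the article separates them for event outcomes.

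If event rates fall only while the team is visiting, the annual total still falls, and this could be reported as reduced use following the MBC. If benefit appears only later, the total understates it. A reader of the total cannot tell which has happened. This matters because the article presents long-term outcome as its contribution and argues that sustained benefit may be more important than a short-term response.

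**Working it through.** **Inputs.** Programme length is 9 weeks (intervention description, Table 1). The after-window is 12 months from enrollment, taken as 52 weeks (Statistical Analysis Plan). Data updates are at 6 and 12 months from enrollment (Health Care Resource Use Outcomes). The article gives no event rates, so the rate ratios below are assumptions.

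**Step 1: the plan's own figure.** Counted from enrollment, 12 months is 52 weeks. The stated follow-up reproduces.

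**Step 2: post-programme time.**
- 52 − 9 = 43 weeks, and 43/52 × 12 = 9.9 months.
- Programme share of the window: 9/52 = 17.3%.
- This assumes that enrollment coincides with Week 1. The gap is not stated. If enrollment precedes Week 1 by 1 to 4 weeks, 42 to 39 weeks remain.

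**Step 3: the 6-month update.** It is also counted from enrollment. Of its 26 weeks, 9 (9/26 = 35%) are programme and 17 are not. The second half-year is wholly post-programme, but the stated comparison uses only the 12-month values.

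**Step 4: what the annual total would show.** With rate ratio a during the programme and b afterwards, each relative to the participant's usual rate and with events otherwise spread evenly:

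annual ratio = (9a + 43b)/52

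| Assumed a | Assumed b | Calculation | Annual ratio |
|---|---|---|---|
| 0.50 | 1.00 | (4.5 + 43)/52 | 0.913 |
| 1.00 | 0.80 | (9 + 34.4)/52 | 0.835 |
| 1.00 | 0.70 | (9 + 30.1)/52 | 0.752 |
| 1.00 | 0.50 | (9 + 21.5)/52 | 0.587 |

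The first row is an apparent 8.7% reduction with nothing lasting. In the other rows the total shows 43/52 = 83% of the true later reduction; a 30% reduction appears as 24.8%.

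**Step 5: the questionnaires.** Scores at 9 and 52 weeks are separate measurements, so the end-of-programme response and its later persistence can be told apart. The problem is confined to the event outcomes.

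**The case against.** The strongest reply is that nothing is misstated. The window is openly anchored at enrollment, and the article never claims 12 months after completion. A reader might infer from the durability wording that 12 months of post-programme follow-up is being claimed, or that the 12-month figure is wrong. The documents support neither reading, and this part of the reply stands in full.

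The anchor is also a good one. It gives two adjacent windows of equal length, balances season, and does not condition on finishing the programme. That stands too, and the annual total should remain the main comparison.

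Third, the article's emphasis on sustained benefit is chiefly about symptoms, which the 9- and 52-week assessments already separate. This stands for the scores. It does not cover health care use and exacerbations, which Study Design lists under the same follow-up as durability.

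Fourth, the update at 6 months would allow a wholly post-programme look at the second half-year. That is true, but no such comparison is stated, and it would leave out 17 of the 43 post-programme weeks.

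Fifth, a Week 9 boundary needs event dates. Strengths and Limitations admits that patient recall of exacerbations is poor and that rescue prescriptions make their timing harder to establish. This stands for community-treated exacerbations. It has less force for emergency department visits and admissions, which are checked against local hospital records.

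Finally, a secondary split by period could be left to a full analysis plan that is not shown. Its absence is not the point. The point is that the comparison the article does state does not match the aim and durability wording it also states.

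**Conclusion.** The enrollment-anchored comparison is sound and should stay. What it cannot do alone is support a statement that reduced health care use or exacerbations persist after the programme, because about 17% of its window is the programme. About 43 weeks follow it, or somewhat fewer if enrollment precedes Week 1.

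The likely distortion is modest. In the illustrations it is a spurious reduction of just under 9% in one direction, or a loss of about one-sixth of a true later reduction in the other. Both rest on assumed rate ratios, and the direction cannot be known from the annual total. The second illustration may be the less plausible, since assessment and the first strategies come in Week 2 and benefit could begin during the programme.

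The primary outcome, CRQ mastery, and the durability of the other breathlessness scores are not affected. This is an inexpensive improvement to a secondary analysis and its wording, not a flaw in the main design.

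**What to change.** 1. Keep the 12-month total before and after enrollment as the main comparison.
2. Before the health care use analysis is run, prespecify a supplementary split of emergency department visits, unplanned hospitalizations and bed days into enrollment to Week 9 and Week 10 to Week 52, as rates per person-time. The article reports data analysis as ongoing; if this comparison has already been run, label the split post hoc.
3. Set the Week 10 to Week 52 period against the same calendar weeks of the prior year, so that season stays balanced.
4. Rest any durability statement about health care use on that second period.
5. Treat the same split for self-reported community exacerbations as exploratory, because of the dating problem the article acknowledges.
6. Reword the aim and the durability text to say that follow-up is 12 months from enrollment, about 43 weeks of it after the programme.

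**Cost.** One extra table and some wording. No new data collection should be needed where hospital records date the events. The 9-week stratum will hold few events, the post-programme estimate will be somewhat less precise than the annual one, and the stated post-programme follow-up becomes shorter. The split does not cure the general limits of an uncontrolled before-and-after comparison, which the article already acknowledges.
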